**3.4 RUTF supplement**

### RUTF item

RUTF is designed for catch up growth in malnourished children and therefore RUTF is also expected to promote catch up growth and weight gain after a period of anorexia. In this study, Plumpynut® will be the RUTF provided. Of the RUTF’s available, Plumpynut® is the most widely accepted and it has proven effects on child growth.[[22]](#endnote-19), [[23]](#endnote-20), [[24]](#endnote-21)

### Quantity

The 1996 supplementation studyprovided a fortified food ad libitum. The average consumption was 117 kcal/kg/day, and the average study subject weight was between 6.8 and 7.7 kg; this means a total supplement of 796 to 900 kcal/day was given. 10

MSF has chosen to provide a fixed quantity supplement, as currently packaged and used in existing programmes. This contains 500 kcal/day. Although this supplement has a lower energy value than the study in Gambia, it is liked by children and of very high quality. In addition, the energy (calories) provided is not the only criteria for supplementation, as lack of catch up growth also depends on the availability of micronutrients. The supplement must provide at least 1 RDI (Recommended Daily Intake) of the anti oxidant vitamins and minerals important for the production of erythrocytes (Vitamin A, B, C, selenium, zinc, folic acid, copper, iron). One package of Plumpynut® provides about 1 RDI (see annex 6).

# 4. CASE DEFINITION AND MAIN OUTCOME MEASURES

**4.1 Diagnosis**:

Malaria caused by *P. falciparum* will be diagnosed using a step- wise approach:

1. Screening for clinical signs of malaria
2. Rapid test (Paracheck®)
3. Laboratory confirmation.

During the initial screening of children presenting at the clinic, those with fever >38 degrees and/or a history of fever within the past 2 days will have a rapid test (Paracheck®) performed.[[25]](#endnote-22) Other symptoms that might be related to a malaria infection (e.g. anaemia, splenomegaly, headache) can indicate a Paracheck® to confirm malaria. Cases with a negative Paracheck® will be excluded. In order to exclude false positive Paracheck® test results (the test may remain positive for up to 6 weeks), a positive Paracheck® will be followed by laboratory confirmation (thick blood film). Those with no parasitaemia will be excluded.

In children with a positive blood film for *P. falciparum,* clinical signs will be assessed to exclude severe (complicated) malaria. If anaemia is clinically suspected the haemoglobin will be measured to exclude severe anaemia. Those children with a positive Paracheck®, positive blood film for *P. falciparum* and no other exclusion criteria will be eligible for the study and their caregivers will be asked for consent to enrol.

**4.2 Outcome parameters:**

**Main outcome:**

Average weight gain (g/kg/day) in the intervention group from day 1 to day 14 will be compared with the average weight gain in the control group.

**Secondary outcomes:**

- Proportion of children having lost weight in each group
- Sustained weight gain compared to short term weight gain (as assessed at 2 weeks after completion of the supplementation period (i.e. 4 weeks post intervention)
- Contributing factors for weight change (see details of potential confounders/effect modifiers in the following section).

# 5. CONFOUNDING FACTORS

There are many factors potentially influencing weight gain or loss other than a given supplement. These confounders may influence the study outcome. In reviewing previous literature, the following known confounders for convalescence15 or for the relationship between malaria and nutritional status6, 9, [[26]](#endnote-23) will be measured:

- Duration of the complaints before attending the clinic [[27]](#endnote-24)
- Duration of symptoms of malaria before attending the clinic
- Age of child (effect modifier 23); as age may be unreliable length/height can be used as a matched variable
- Breastfeeding (partial, as exclusive breastfed children are excluded)
- Disease history (e.g., respiratory tract infections, diarrhoea, vomiting, anorexia) during the last 2 weeks before enrolment
- Incident diseases during the study period
- Socio-economic status of the family
- Educational status of the caretaker and head of the household
- Maternal age
- Nutritional status at baseline
- Being resident or displaced.

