# *Consent forms are presented in Annex 1.*

| Annex 3: RUTF for malaria recovery study |
| --- |
| **Intake questionnaire upon enrolment** |

| Date (dd/mm/yy): |  |  | | | |  | |  |  | |  | | | |  |
| --- | --- | --- | --- | --- | --- | --- | --- | --- | --- | --- | --- | --- | --- | --- | --- |
| Patietn ID |  |  | | | |  | |  |  | |  | | | |  |
|  |  |  | | | |  | |  |  | |  | | | |  |
|  |  |  | | | |  | |  |  | |  | | | |  |
|  |  |  | | | |  | |  |  | |  | | | |  |
| Sex | Male | | Female | | |  | |  |  | |  | | | |  |
|  |  |  | | | |  | |  |  | |  | | | |  |
| **Part 1: Questions concerning your child** | | | | | | | |  |  | |  | | | |  |
|  |  |  | | |  | | |  |  | |  | | | |  |
| 1. What is the exact age of your child? | | | | | | | |  |  | |  | | | |  |
|  |  | Birth date of child (dd/mm/yy) | | | | | |  |  | |  | | | |  |
|  | ***Or*** | Age of child (months, years). | | | | | |  |  | |  | | | |  |
|  |  |  | | |  | | |  |  | |  | | | |  |
| 2 You have brought your child because he/she is ill. How many days ago did this episode of illness start? | | | | | | | | …… | days | |  | | | |  |
|  |  |  | | |  | | |  |  | |  | | | |  |
|  | | | | | | | |  |  | |  | | | |  |
| 3. Has your child been ill with a fever at any time in the last 2 weeks? | | | | | | | | Yes |  | |  | | | |  |
|  |  |  | | |  | | | No |  | |  | | | |  |
|  |  |  | | |  | | | Don’t know |  | |  | | | |  |
|  |  |  | | |  | | |  |  | |  | | | |  |
|  |  |  | | |  | | |  |  | |  | | | |  |
| 4. Has your child had an illness with cough at any time in the last 2 weeks? | | | | | | | | Yes |  | |  Q 5 | | | |  |
|  |  |  | | |  | | | No |  | |  Q 7 | | | |  |
|  |  |  | | |  | | | Don’t know |  | |  Q 7 | | | |  |
|  |  |  | | |  | | |  |  | |  | | | |  |
|  |  |  | | |  | | |  |  | |  | | | |  |
| 5. When your child had an illness with a cough, did she/he breathe faster than | | | | | | | | Yes |  | |  Q 6 | | | |  |
| usual with short, rapid breaths or have difficulty breathing? | | | | | | | | No |  | |  Q 7 | | | |  |
|  |  |  | | |  | | | Don’t know |  | |  Q 7 | | | |  |
|  |  |  | | |  | | |  |  | |  | | | |  |
| 6. Was the fast or difficult breathing due to a problem in the chest or | | | | | | | | Chest only | | |  | | | |  |
| to a blocked or runny nose? | | | | | | | | Nose only | | |  | | | |  |
|  |  |  | | |  | | | Both | | |  | | | |  |
|  |  |  | | |  | | | Don’t know | | |  | | | |  |
|  |  |  | | |  | | | Other; specify | | |  | | | |  |

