|  |  |  | | |  | | |  |  | |  | | | |  |
| 7. Has your child had diarrhoea in the last 2 weeks? | | | | | | | | Yes |  | |  | | | |  |
| *(Explain the definition of diarrhoea: at least 3 or more liquid stools per day )* | | | | | | | | No |  | |  | | | |  |
|  |  |  | | |  | | | Don’t know |  | |  | | | |  |
|  |  |  | | |  | | |  |  | |  | | | |  |
| 8. In the last 2 weeks, has your child vomited everything? | | | | | | | | Yes |  | |  | | | |  |
| (persistent vomiting several times) | | | | |  | | | No |  | |  | | | |  |
|  |  |  | | |  | | | Don’t know |  | |  | | | |  |
|  |  |  | | |  | | |  |  | |  | | | |  |
| 9. Do you currently breast-feed your child? | | | | | | | | Yes |  | |  Q 10 | | | |  |
|  | | | | | | | | No |  | |  Q 11 | | | |  |
|  | | | | | | | |  |  | |  | | | |  |
|  | | | | | | | |  |  | |  | | | |  |
| 10. How many times during the day did you breastfeed yesterday? | | | | | | | | …… times | | | | | |  |  |
|  | | | | | | | |  | | | | | |  |  |
| 11. **Since your child was ill**, did she/he eat (food or breast milk) | | | | | | | | Much less | | | | | |  |  |
| less then usual, about the same amount, or more than usual? | | | | | | | | Somewhat less | | | | | |  |  |
| IF LESS, PROBE: Was he/she eating much less than usual or somewhat less? | | | | | | | | About the same | | | | | |  |  |
|  | | | | | | | |  | | | | | |  |  |
|  | | | | | | | | Somewhat more | | | | | |  |  |
|  | | | | | | | | Much more | | | | | |  |  |
|  | | | | | | | | Don’t know | | | | | |  |  |
|  | | | | | | | |  |  | | |  | | |  |
|  |  |  | | |  | | |  |  | | |  | | |  |
| **Part 2: The following questions concern yourself or the entire family** | | | | | | | |  |  | | |  | | |  |
|  | | | | | | | |  |  | | |  | | |  |
|  | | | | | | | | Mother | | | |  | | |  |
| 12: What is your relation to the child? | | | | | | | | Father | | | |  | | |  |
|  | | | | | | | | Grandparent | | | |  | | |  |
|  | | | | | | | | Brother /sister | | | |  | | |  |
|  | | | | | | | | Other | | | |  | | |  |
| 13. What is your own age? (years) …………..years | | | | | | | |  | | | |  | | |  |
|  | | | | | | | |  | | | |  | | |  |
| 14. Where (in what village) do you currently live? ………………………………………….. | | | | | | | |  | | | |  | | |  |
|  | | | | | | | |  |  | | |  | | |  |
| 15.How long have you lived in Dubie or surroundings of Dubie? | | | | | | | | Always | |  | |  Q 17 | | |  |
|  | | | | | | | | …… …. | |  | | Years | | |  |
|  | | | | | | | |  |  | |  | | | |  |

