| 16. Were you displaced because of the war? | | | | | | | | Yes | | | |  | | |  |
|  | | | | | | | | No | | | |  | | |  |
|  | | | | | | | | Don’t | know | | |  | | |  |
|  | | | | | | | |  |  | | |  | | |  |
| 17. What is the highest level of education that you have completed? | | | | | | | |  |  | | |  | | |  |
| *Please tick the box of the highest level of education* | | | | | | | |  |  | | |  | | |  |
|  |  | No formal schooling | | | | | |  |  | | |  | | |  |
|  |  | 1-4 years of primary school | | | | | |  |  | | |  | | |  |
|  |  | More than 4 years primary school (but not completed) | | | | | |  |  | | |  | | |  |
|  |  | Primary school completed | | | | | |  |  | | |  | | |  |
|  |  | 1-3 years Secondary school (but not completed) | | | | | |  |  | | |  | | |  |
|  |  | Secondary school completed | | | | | |  |  | | |  | | |  |
|  |  | High school | | | | | |  |  | | |  | | |  |
|  |  | College/pre-university/University (but not completed) | | | | | |  |  | | |  | | |  |
|  |  | College/pre-university/University completed | | | | | |  |  | | |  | | |  |
|  |  | Don’t know | | | | | |  |  | | |  | | |  |
|  | | | | | | | |  |  | | |  | | |  |
| 18. What is your current marital status? | | | | | | | |  | | | |  |  | |  |
|  |  |  | | | | | Single |  |  Q 21 | | | | | |  |
|  |  |  | | | | | Currently married |  |  Q 19 | | | | | |  |
|  |  |  | | | | | Cohabiting |  |  Q 19 | | | | | |  |
|  |  |  | | | | | Divorced/Separated |  |  Q 21 | | | | | |  |
|  |  |  | | | | | Widowed |  |  Q 21 | | | | | |  |
|  | | | | | | | |  | | | |  | | |  |
| 19. Is your husband/partner living with you now or is he staying elsewhere? | | | | | | | | Living with her/him | | | |  | | |  |
|  | | | | | | | | Staying elsewhere | | | |  | | |  |
|  | | | | | | | |  | | | |  | | |  |
| 20. What is your husbands’/ partners occupation. That is, what kind | | | | | | | | Agriculture | | | |  | | |  |
| of work does he mainly do? | | | | | | | | Trading/shop | | | |  | | |  |
|  | | | | | | | | Regular job | | | |  | | |  |
|  | | | | | | | | Other , specify | | | |  | | |  |
|  | | | | | | | |  | | | |  | | |  |
| 21. What is your occupation, that is, what kind of work do you mainly do? | | | | | | | | Agriculture | | | |  Q22 | | |  |
|  | | | | | | | | Trading/shop | | | |  Q23 | | |  |
|  | | | | | | | | Regular job | | | |  Q23 | | |  |
|  | | | | | | | | Other , specify | | | |  Q23 | | |  |
|  | | | | | | | |  |  | | |  | | |  |

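### Annex 3 does not record three Section 5 factors as listed: head-of-household education, maternal age when the mother is not the respondent, and a separate duration of malaria symptoms

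*Protocol*

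**What the plan says.** Protocol Section 5 introduces its list as "the following known confounders for convalescence15 or for the relationship between malaria and nutritional status6, 9" and commits the trial to measuring every factor on it. There are eleven. Four matter here:

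- education, worded as "Educational status of the caretaker and head of the household";
- maternal age;
- duration, listed twice: once for the complaints in general and once as "Duration of symptoms of malaria before attending the clinic";
- breastfeeding (partial, because exclusively breastfed children are excluded).

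Annex 3 is the questionnaire given at enrolment. Its relevant items are:

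- Question 2: "How many days ago did this episode of illness start".
- Question 9: "Do you currently breast-feed your child". A negative answer skips question 10, which asks how often.
- Question 12: "What is your relation to the child", with mother, father, grandparent, sibling and other as answers.
- Question 13: "What is your own age? (years".
- Question 17: "What is the highest level of education that you have completed".

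Section 6.1 lists the admission data. Under medical history it names one symptom duration and whether breastfeeding is exclusive or partial. It names neither maternal age nor anyone's education.

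**The concern.** The list and the form that should fill it do not match. Section 5 describes characteristics of the mother, the household head and the malaria episode. Annex 3 asks mostly about whoever brought the child. The protocol expects that this will not always be the mother: question 12 offers four other answers, Section 3.2.1 accepts consent from a parent or guardian, and Annex 2 accepts a guardian who is a close relative.

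The contribution of these factors to weight change is the fourth specific objective in Section 2 and a secondary outcome in the synopsis and Section 4.2. The data-analysis text in Section 10 draws its adjustment variables from confounders identified in previous studies, which is also how Section 5 describes its list. A separate statistical analysis plan could not repair the gap, because it can only use what the form collected.

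**Working it through.** No arithmetic in the protocol is at issue. The check sets each factor against every place that could supply it: Annex 3 (questions 1 to 29), Annex 2, Annex 4, Section 6.1 and the activity schedule.

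| Section 5 factor | Annex 3 | Elsewhere | Result |
|---|---|---|---|
| Education of caretaker | Question 17, respondent's own | None | Recorded if the respondent is the caretaker |
| Education of head of household | None; question 20 asks the partner's occupation only | None | Known only if the respondent is the head, and the form does not record whether that is so |
| Maternal age | Question 13, respondent's own | None | Recorded if question 12 is answered as mother; otherwise missing |
| Duration of complaints | Question 2 | Section 6.1, one duration | Recorded |
| Duration of malaria symptoms | None; question 3 asks whether there was fever in the last 2 weeks, without onset | Section 6.1, the same single duration | Not separable from the row above |
| Partial breastfeeding | Questions 9 and 10, addressed to the respondent | Section 6.1, medical history; Annex 2 item D4 for exclusive breastfeeding | Recorded, with a wording risk for non-mothers |

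**Education.** Without an item that identifies the household head, the analyst cannot tell which answers to question 17 belong to a head. That half of the factor is unusable, including for children whose respondent happens to be the head.

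**Maternal age.** Questions 12 and 13 together show exactly when the recorded age is not the mother's, so the value is identifiably missing. The protocol does not give the share of non-mother respondents. Assuming 10% to 30%, maternal age would be missing for 0.10 × 200 = 20 to 0.30 × 200 = 60 of the planned 200 children.

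**Duration.** A child with a week of cough and two days of fever contributes one number. Which of the two Section 5 durations that number represents is left to the respondent.

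**Breastfeeding.** Annex 5 sets the analysis cut-off on question 10, at 2 times per day. If a father or grandparent takes question 9 literally and answers no, the form skips the item on which that cut-off depends.

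**The case against.** Four counter-arguments deserve weight.

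*Annex 3 is not the only admission record.* It has no field for weight, height, MUAC or parasitaemia, so another form must exist. The activity schedule also lists medical history separately from the intake form, and Section 6.1 places symptom duration and breastfeeding there. This stands for breastfeeding: one cannot say that it would be lost. It does not rescue the second duration, because Section 6.1 also names only one. Nor does it help with maternal age or the household head's education, which Section 6.1 does not mention.

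*Question 2 is a fair measure of malaria duration.* Every enrolled child has slide-confirmed *P. falciparum*, and the question concerns the current episode. This stands. A reader might infer that the synopsis example, duration of malaria before treatment, goes unmeasured. The documents do not support that; what is lost is the separation of two closely related durations.

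*Trained staff and a pre-test would catch the wording of question 9.* Annex 5 says the question is meant to capture breastfeeding at the day of interview, and an interviewer may take it that way. So question 9 carries a risk of miscoding, and a reader should not infer that every child brought by a non-mother will be coded as not breastfed.

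*The consequences are small.* Allocation is randomised, and Section 10 adjusts only for confounders that also prove significant. This stands, and it limits the point to secondary results. It does not remove the gap between what Section 5 promises and what the form asks.

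**Conclusion.** The mismatch is confirmed in a limited form. Of eleven Section 5 factors, three are not collected as listed: education lacks the household head, maternal age is missing when a non-mother answers, and malaria-symptom duration cannot be separated from duration of complaints. Breastfeeding carries a wording risk only.

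Two stronger conclusions are tempting and should not be drawn. The first is that the treatment comparison is biased. These are baseline characteristics in a randomised trial, and an incomplete covariate does not bias the comparison between arms. The second is that a maternal-age effect would be diluted by grandparents' ages. That happens only if the analyst ignores question 12 and treats every respondent's age as the mother's, and nothing in the protocol plans this.

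What remains affects the fourth specific objective, the matching secondary outcome and the candidate covariates. The number of children affected depends on how often non-mothers answer, which the protocol does not state. The conclusion also assumes that the admission record not shown holds no more than Section 6.1 lists. The point merits correction because the data cannot be recovered later and the change is easy now.

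**What to change.** Change Annex 3 before the pre-test described in Section 8:

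- beside question 13, add the age of the child's mother in years;
- beside question 17, add the same education grid for the head of household;
- beside questions 2 and 3, add the number of days since the fever began;
- reword questions 9 and 10 to ask whether the child is currently breastfed and how many times the child was breastfed yesterday, whoever answers.

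Use these fields, not the respondent's own details, for the Section 5 factors. The respondent's education still serves for the caretaker.

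If the sponsor does not want the extra items, align Section 5 with what Annex 3 records: respondent's education, maternal age where the mother responds, and one illness duration. The wording of questions 9 and 10 should be changed either way.

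The cost is three added questions, two rewordings and a slightly longer interview. Sample size, visits and the primary analysis do not change.

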# 6. DATA COLLECTION

**6.1 Admission**

On admission, a questionnaire will be administered (see annex 3), and anthropometry, medical examination, and lab tests performed:

- Demographics: Name, age, address
- Anthropometry: height, weight, MUAC, oedema
- Medical status: fever, danger signs for severe malaria, loss of appetite, concomitant illnesses
- Laboratory data: RDT result, thick blood film and level of parasitaemia
- Medical history: duration of symptoms, breastfeeding (exclusive or partial), appetite
- Socio-economic: main source of income, whether receiving food aid, number of meals consumed.

**6.2 Day 14 after treatment**:

At day 14 a further questionnaire (see annex 4) will be administered, in addition to anthropometry measurements and repeat medical examination:

- Anthropometry: weight, MUAC, oedema
- Medical status: fever, appetite, intercurrent illnesses,
- Laboratory data: thick blood film and level of parasitaemia
- Medical history: duration of symptoms, new illnesses.

**6.3 Day 28:**

At day 28 a further questionnaire (see annex 4) will be administered, in addition to anthropometry measurements and repeat medical examination:

- Anthropometry: weight, MUAC, oedema
- Medical status: fever, appetite, intercurrent illnesses
- Medical history: new illnesses.

# 7. QUALITY CONTROL

**7.1 General:**

An additional expatriate research supervisor will be assigned for 3,5 months to give training, and supervise and monitor the implementation of the study. Clinical procedures and data collection and will be evaluated regularly by the research supervisor to ensure that the protocol is being followed correctly. Patient records will be double checked on a random basis. A random sample of interviews and clinical procedures will be observed, and the Paracheck® procedure will be evaluated according to a standard checklist.

**7.2. Staff, Training, and Supervision**

There will be 4 additional staff for 2 months to ensure adequate assessments at admission, discharge and follow-up of defaulters, for monitoring during the treatment phase and for performing the laboratory work. As the staff will not be blinded for selection of participants or for allocation of the supplement the potential exists for observer bias. This will be addressed by selecting staff- to be responsible for the interviews- who are not currently involved in health care provision within MSF clinics or having regular duties in the clinic.

Training of identified staff on the aims and procedures of the study and role of staff will take place before the study starts by the expatriate field research supervisor. Staff will be trained including practical demonstration of their specific tasks, such as interviews, weight measurements, and laboratory techniques (including the correct use of Paracheck®)

**7.3 Weight changes**

Weight gain is defined as the difference in weight between weight on day one and weight on day 14. The weight of an individual varies during the day and therefore ideally weight should be measured at the same time of the day on each follow up visit. As patients may initially present at any hour during the day, their enrolment in the study and the first weight taken will be at any time on this day (day 0). In order to standardise the time of taking weight, to limit intra-day variation, patients will be asked to come back for follow up within a certain period in the day (pre or post meal times). The follow up visits will be scheduled at the same period of the day. The weight at day 1 (the day after enrolment) will be used as baseline.

Weight changes in a short period are very small. Therefore even a small degree of measurement error could influence outcomes. By weighing each individual twice with two independent observers, measurement error will be calculated and the average will be taken for the analysis. Electronic weighing scales will be used (SECA 834 and 835) that have a precision of >=20g.

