**Number of patients:**

100 patients provided with 92 g (500 kcal) Plumpynut® (aReady To Use Therapeutic Food (RUTF)) for 14 days, and 100 patients not provided with RUTF.

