# 3. STUDY DESIGN AND METHODS

**3.1 Study design**

The study design is that of a randomised intervention study. Children with confirmed *P. falciparum* malaria, meeting all study inclusion criteria, will be enrolled in the study for a period of 28 days. Participants will be assigned at random to either the intervention or the control group.

The intervention group will receive treatment for malaria plus 1 bag of RUTF per day for 14 days. The control group will receive treatment for malaria without provision of RUTF.

Random allocation to either intervention or control group is thought to be acceptable by the population as RUTF is seen as a medicine rather than a food item. A similar study did not meet a problem with randomisation.[[18]](#footnote-2) For other illnesses, the participants will be offered medical treatment according to the best local standards.

Follow-up visits will be scheduled for directly observed treatment for malaria (day 0, 1 and 2), malaria parasite density and clearance (D0, D2, and until slide is negative; and for weight measurements at day 0, 1, 13 and 27. Weight will be measured twice at each visit by two independent observers. A detailed questionnaire will be conducted at the start, and at day 13 and 27.

All participants who attend follow up sessions at the clinic will receive a small incentive[[19]](#footnote-3)* in order to compensate for lost time due to participation in the study (RUTF will not be given to the control group at the end of the study).

The study will be conducted in the period (May-June) that is likely to have a stable prevalence of malnutrition, a stable incidence of *P. falciparum* malaria and other morbidities (e.g. pneumonia and diarrhoea). The total duration of the data collection will be 2 months for data gathering: 4 weeks of enrolment (40 participants per week) and 4 weeks of follow up (the last follow-up being done 4 weeks after the last enrolment).

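### Section 7.3 fixes the time of day for weighing but not its timing relative to the day's RUTF sachet, so sachet content may enter the 2-week weight contrast

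*Protocol*

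**What the plan says.** Section 7.3 recognises that weight varies within the day. It sets aside the day-0 weight, taken at whatever hour the child presents, and states that "The weight at day 1 (the day after enrolment) will be used as baseline". For later visits, "patients will be asked to come back for follow up within a certain period in the day (pre or post meal times"), and "The follow up visits will be scheduled at the same period of the day". Two observers weigh each child independently and the average is used. The section gives its reason: over so short a period "even a small degree of measurement error could influence outcomes".

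On the supplement, section 3.1 says "The intervention group will receive treatment for malaria plus 1 bag of RUTF per day for 14 days", and the synopsis gives the daily quantity: "100 patients provided with 92 g (500 kcal) Plumpynut".

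On the day of the 2-week weight the protocol gives two answers. Section 3.1 schedules visits "for weight measurements at day 0, 1, 13 and 27". Section 7.3 says "Weight gain is defined as the difference in weight between weight on day one and weight on day 14", and section 4.2 also defines the main outcome from day 1 to day 14.

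No section requires fasting, an interval since the last meal or sachet, or weighing before that day's sachet. Annex 4 asks the RUTF arm how many sachets were eaten and how many empties were returned, but not when the last one was eaten.

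**The concern.** Weighing each child at the same period of the day balances the gut content of ordinary meals, which both arms eat. It does not by itself balance a food that only one arm receives. If the chosen period may follow a meal and the 2-week weight falls on a supplementation day, a child in the RUTF arm may be weighed with part or all of a sachet, and any water taken with it, still in the gut. Double weighing cannot detect this, because both observers weigh the same child in the same state.

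Two results could be affected. The first is the 2-week difference between arms, where this mass would be read as growth. The second is the comparison of 2-week with 4-week gain (section 4.2, secondary outcomes; section 10, data analysis). By day 27 the ration has ended, so mass present at 2 weeks and gone at 4 weeks would look like weight lost after supplementation. The stated objective is to find to what extent RUTF promotes growth, so the size of the estimate matters as well as its significance.

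**Working it through.** **Inputs.** Section 3.3: control gain 0.09 kg (SD 0.44), intervention gain 0.44 kg (SD 0.33), two-sided 5%, 80% power, 20% loss, 100 per group proposed, 80 called realistic. Synopsis: 92 g per sachet. Section 3.4: mean weight 6.8 to 7.7 kg in the cited supplementation study.

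**The plan's own figures.** The planned difference is 0.44 − 0.09 = 0.35 kg.
- Printed formula: 2 × (1.96 × 0.44 / 0.35)² = 12.14, so 13, as stated.
- Unequal variances: (0.44² + 0.33²) × (1.96 + 0.8416)² / 0.35² = 19.38, so 20, as stated.
- Loss to follow-up: 20 × 1.2 = 24, as stated.

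**When each weight is on supplement.** Fourteen daily sachets cover days 0–13 or days 1–14, depending on the first RUTF day.

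| First sachet | 2-week weight | Day-1 baseline | 2-week weight on supplement? | Artefact in the change |
|---|---|---|---|---|
| Day 0 | Day 13 | on supplement | yes | largely cancels |
| Day 0 | Day 14 | on supplement | no, ration finished | none in favour of RUTF |
| Day 1 | Day 13 or 14 | first sachet may follow weighing | yes | up to one sachet |

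Day 13 is a supplementation day under either start. Day 14 is one only with a day-1 start. Day 27 is off supplement in every case.

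**Upper bound.** Suppose every RUTF child has one whole sachet in the gut at 2 weeks, none at baseline, and has eaten no less ordinary food. The artefact is then 92 g before water, and 92 / 350 = 26% of the planned difference. On the outcome's scale, over 12 or 13 days:
- 92 g is 92 / (7.7 × 13) = 0.92 to 92 / (6.8 × 12) = 1.13 g/kg/day;
- 350 g is 350 / (7.7 × 13) = 3.50 to 350 / (6.8 × 12) = 4.29 g/kg/day.

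These conversions assume the cited study's body weights apply here. The 26% does not depend on body weight.

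**Effect on the test if there is no true difference.** The net mass b is not in the documents, so it is varied over the whole range. SE = √((0.44² + 0.33²) / n), which is 0.055 kg at n = 100 and 0.0615 kg at n = 80. The two-sided rejection probability is 1 − Φ(1.96 − b/SE) + Φ(−1.96 − b/SE).

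| Net mass b | Share of 350 g | n = 100 per group | n = 80 per group |
|---|---|---|---|
| 0 g | 0% | 5% | 5% |
| 23 g | 7% | 7% | 7% |
| 46 g | 13% | 13% | 12% |
| 69 g | 20% | 24% | 20% |
| 92 g | 26% | 39% | 32% |

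This uses an unadjusted comparison of means with the planned SDs. At a true difference of 350 g, power exceeds 99.9% at either sample size.

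**The case against.** A reader might infer that the primary effect is inflated by the weight of a sachet, in one arm only. The documents do not support that, for three reasons.

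- **Start day.** If RUTF begins on day 0, the day-1 baseline is also on supplement, and the same-period rule tends to cancel the sachet between the two weights. Annex 4 leans this way: on day 13 it asks how many sachets were eaten over the preceding 14 days, and 14 days ending on day 13 are days 0 to 13. Annex 7 marks when RUTF is given, but its columns cannot be read in the text at hand, and that is not an error in the plan.
- **Day of weighing.** Under the day-14 definition with a day-0 start, the weight falls after the last scheduled sachet.
- **Size.** 92 g is a ceiling. Controls eat meals too, and a 500 kcal sachet may replace part of one, so the net excess could be far smaller.

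It is equally tempting to say that sustained gain is understated. Section 2 measures that from presentation to four weeks, which does not use the 2-week weight. Only the 2-week versus 4-week comparison is exposed.

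It can also be argued that this is weighing-procedure detail. Section 7.3 already controls the period of the day, the mention of meals may describe only how that period is chosen, and sections 7.1 and 7.2 provide training and observation.

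All of this limits the point without removing it. Cancellation is not assured. Section 7.3 permits a post-meal period, and nothing in the protocol orders weighing against the sachet or records what would be needed to check afterwards.

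**Conclusion.** The point holds as a possible artefact, not an established bias. As written, the plan can leave sachet content in the RUTF arm's 2-week weight. The net bias in favour of RUTF is unknown and lies between about 0 and 92 g before water, or 0 to 26% of the planned difference. The upper end needs a whole sachet at follow-up, none at baseline and no displaced food. The lower end applies if the baseline also follows a sachet, if the weight is taken on day 14 after the ration has ended, or if the sachet replaces other food.

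Detection of the planned 350 g effect is not at risk. What could be affected is the size of the estimate, the interpretation of a small true effect, and the 2-week versus 4-week comparison. Section 3.4 notes that this ration supplies less energy than the one behind the 350 g assumption. If the true effect is smaller, any fixed artefact is a larger share of it. Severity: minor.

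**What to change.** In section 7.3, replace the option of a period before or after meals with one rule for both arms. At the baseline (day 1), 2-week and 4-week visits, every child is weighed in a pre-meal period and before any sachet is eaten that day. Record the time since last food or sachet beside each weight. This belongs on the weight record, because Annex 4 is not used on day 1. The recorded interval also allows a check for food eaten the evening before, which the rule does not cover.

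Reconcile day 13 in section 3.1 with day 14 in sections 4.2 and 7.3, and state in the text the first RUTF day relative to the day-1 baseline weight. Those two facts decide whether each weight is on supplement.

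The cost is one sentence in section 7.3, one instruction to caretakers and one form field. The sample size does not change. The downside is that visits are confined to a pre-meal slot, which may lengthen waiting at the clinic.
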